### Participant flow

Figure 2 illustrates the trial flowchart.

**Fig. 2 Fig2:**
[figure not shown]
Participant flow. GP, general practitioner; HCP, healthcare professional

#### Screening and informed consent

Participants who are interested in taking part will contact the research team. A researcher will assess eligibility based on the full inclusion and exclusion criteria, verbally provide information as described in the participant information sheet and answer any questions about participation in the study. Those who are eligible will be booked into an initial face-to-face baseline study visit at their GP practice. When the participant attends the baseline visit, the researcher will provide verbal and written information about the trial and seek informed consent (see Table 1 for the schedule of procedures). Having had a chance to ask questions, those individuals willing to participate will give written informed consent by means of a participant-dated signature. The consent form will also be dated and signed by the researcher who presented and obtained the informed consent.

**Table 1 Tab1:** Schedule of study visits, assessment and procedures

	Screening phone call	Enrolment and baseline (Visit 1)	Allocation	Intervention (Visit 2)	Accompanied shop (Visit 3)	Followup (Visit 4)
Time point (weeks from baseline)	−1	0	2	2–3	4–9	9–10
Responsibility	Central research team	Central research team	Independent researcher	Healthcare professional	Central research team	Central research team
STUDY PROCEDURES						
Eligibility assessment	✓					
Informed consent		✓				
Baseline assessment including:		✓				
Blood pressure		✓				
Height and weight		✓				
Medical history and medications		✓				
Shopping and diet questionnaire		✓				
Instruction on baseline run-in data collection		✓				
Urine sample collection		✓ (+ up to 2 weeks)				
Randomisation			✓			
Intervention delivery				✓		
Accompanied shop and interview					✓	
Follow-up outcome measures including:						✓
Blood pressure						✓
Medical history and medication review						✓
Intervention acceptability questionnaire						✓
Urine sample collection						✓ ✓ (+ up to 7 days)

#### Baseline

The baseline assessment will be undertaken at the initial baseline visit following informed consent. The researcher will collect clinical measures of height (metres), weight (kilograms), and blood pressure (seated systolic and diastolic blood pressure, measured after 5 min rest and using the mean of the second and third of three readings taken 1 min apart using a validated digital automatic blood pressure monitor, the OMRON M10-IT). The researcher will also record demographic information, relevant medication history and medications (verified through the patient’s electronic clinical record) and details of the participant’s shopping behaviour including the frequency of shopping, the number of people for whom they are shopping, the types of stores or settings most commonly visited for groceries and key influences on purchasing decisions (using an investigator-designed questionnaire).

At the end of the baseline visit participants will be instructed on how to use a mobile phone app to record their grocery shopping throughout the study. The app, called ShopScanner, is linked to a food and nutrient information database to enable recording of the nutrient content of purchased foods. They will also be asked to collect their grocery shopping receipts throughout the study.

#### Baseline run-in period

The baseline period will run for 2 weeks following the baseline assessment visit. Participants will be asked to collect a 24-hour urine sample within this baseline period, for the measurement of urinary sodium excretion (mmol/24-hour). They will also be asked to submit their grocery shopping till receipts for this period to the research team. Participants who return partial baseline data will be prompted, by phone or email, to return all requested data.

Participants will be randomised once the urine sample and baseline shopping data for the baseline period have been provided. Participants who do not complete these measures will not be randomised. Participants randomised to the intervention group will be booked to attend an intervention session with a HCP at their GP practice. Control participants will receive the control intervention leaflet by post.

#### Intervention visit

The intervention will be delivered by a HCP at the GP surgery. Designated HCPs from the surgery will be specifically trained to deliver the intervention and to complete an intervention checklist. This visit will last 20–30 min.

#### Follow-up

All participants will be invited to attend one follow-up assessment 6 weeks after they receive their allocated intervention (either the intervention visit or the control information sent by post). During this visit, a researcher will measure blood pressure and document any changes to relevant medical history or medications. Participants will be asked to complete an investigator-designed questionnaire to assess aspects of the intervention (or control leaflet) they received.

The follow-up questionnaire will collect data on changes in knowledge about dietary salt intake, awareness of salt intake and dietary-salt-related behaviours. Separate questions for each group will assess how helpful the Salt Swap intervention (advice session and Salt Swap app) or control leaflet were (1–5 scale from very unhelpful to very helpful) as well as the specific reasons why it was considered helpful or unhelpful (for the Salt Swap intervention only). The intervention group questionnaire will also collect data on app acceptability (“would you be interested in using a free app like the Salt Swap app if it was publically available in future?”) and frequency of use (always, most of the time, occasionally, never). Both groups will be asked if any other forms of support (e.g. apps, tools, advice or contact with health professionals) were used throughout the study.

Participants will be asked to submit their grocery shopping receipts for the past 6 weeks and to provide a second 24-hour urine sample at this appointment or within a week of their follow-up visit. The research team will be responsible for arranging follow-up visits. Participants will be contacted by phone in the first instance (unless an alternative contact method is requested by the participant). The research team will use text messages to remind participants of their upcoming appointments.

#### Accompanied shop

We will undertake an accompanied grocery shopping trip with a convenience sample of participants (both intervention and control), using the think-aloud method. The aim of this is to understand how the study materials and content influence shopping and wider dietary behaviours, and to assess the barriers to and facilitators of using the Salt Swap app.

Retrospective questioning via a semi-structured interview immediately after the accompanied shop will add depth to the information gathered about the participants’ thought processes and understanding of the role of diet in blood pressure control. This qualitative assessment will be undertaken at staggered time points throughout the study.

### Randomisation

Once participants have provided consent and completed the baseline data collection, the research team will randomise them to one of the two trial arms using computer-generated randomisation. The randomisation will be stratified by general practice using block randomisation in blocks of six. A researcher not involved in taking consent or measuring study outcomes will generate the random number sequence using an online random sequence generator (www.sealedenvelope.com) and assign participants to the intervention groups according to the allocation sequence, to ensure allocation is concealed from the rest of the research team until interventions are assigned. Both the research team and participants will be unaware of the treatment allocation prior to consent.

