## Methods

### Trial design and setting

This trial will be an individually randomised, parallel, two-arm, controlled feasibility trial with a 2:1 (intervention to control) allocation ratio. The primary outcome will be the criteria to progress to a full trial. Process evaluation and analysis of effectiveness outcomes may inform a future trial. Participants will be recruited through five primary care practices in Oxfordshire, UK.

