### Recruitment

Practices will search the electronic health records of registered patients to find people who meet the age and blood pressure inclusion criteria. Prior to sending out the invitation letters, the general practitioner (GP) will screen the search results to ensure that all those identified are medically appropriate to participate in the trial and meet the clinical inclusion criteria. The practice will send potential participants an invitation letter asking them to contact the research team if they are interested in participating; the letter will also include a link to an electronic version of the participant information sheet. GPs may also identify eligible patients opportunistically during routine consultations or via the National Health Service (NHS) Health Check programme. We will aim to randomise 40 participants in the study.

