### Blinding

It is not possible to blind the participants, the clinicians delivering the intervention or the research team to treatment group due to the nature of the intervention. The main trial outcomes are progression criteria and process measures, which are unlikely to be influenced by knowledge of treatment allocation. Intervention effectiveness measures comparing trial arms, which would be used as the primary outcome in a future RCT, are objectively measured outcomes and not open to interpretation by researchers.

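### One fixed, stated block size of six within each practice lets an unblinded team deduce about one allocation in five, before a randomisation step that waits on returned baseline data

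*Protocol article*

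**What the plan says.** The Randomisation section of the protocol article sets the method: "The randomisation will be stratified by general practice using block randomisation in blocks of six". Trial design and setting describes a "two-arm, controlled feasibility trial with a 2:1 (intervention to control) allocation ratio", which makes each block four intervention and two control places. There are five strata ("Participants will be recruited through five primary care practices in Oxfordshire, UK") and a target of 40 (Recruitment: "We will aim to randomise 40 participants in the study").

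Two further statements fix the timing and the flow of information:

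- **Entry to randomisation.** Baseline run-in period says "Participants will be randomised once the urine sample and baseline shopping data for the baseline period have been provided". People who return only part of the data are prompted by phone or email, and "Participants who do not complete these measures will not be randomised". Table 1 puts consent at week 0 and allocation at week 2.
- **Knowledge of allocation.** Blinding says "It is not possible to blind the participants, the clinicians delivering the intervention or the research team to treatment group". Table 1 makes the central research team responsible for the baseline visit, the accompanied shop and the follow-up visit.

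There is a safeguard. The Randomisation section gives sequence generation and assignment to a researcher who neither takes consent nor measures outcomes, and says this keeps the allocation hidden from the other researchers up to assignment. Table 1 likewise lists an independent researcher for allocation.

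**The concern.** Keeping the list with a separate person protects the list, but it does not prevent deduction from assignments already made. With one block size of six, known to the team, the rest of a block is fixed as soon as two controls or four interventions have been assigned in that practice. The sixth place of every completed block is fixed in all cases. An unblinded central team that sees every practice's assignments has what it needs to work this out.

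This matters because consent does not settle who is randomised. A consented participant still has to return a urine sample and two weeks of shopping data. How persistently partial returners are chased, what counts as complete, and when a participant is put forward could vary with the arm the team foresees. The arms could then differ in motivation or diligence before treatment starts. That would bias the comparisons of urinary sodium, blood pressure and purchased salt, which are meant to inform a definitive trial. App use could also be raised if more engaged people tended to enter the intervention arm.

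**Working it through.** **Inputs from the protocol article.** Blocks of six within practice (Randomisation); 2:1 ratio and five practices (Trial design and setting); 40 participants (Recruitment).

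**Assumptions.** Eight participants per practice, which the article does not state (other spreads are tried below). The team knows the block size and all earlier assignments in the practice.

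**The plan's own figure.** The article gives no figure for predictability. Its only sample-size figure is the precision of the follow-up rate, which reproduces: 1.96 × √(0.8 × 0.2 / 40) = 0.124, or 80% ± 12%. This point does not affect it.

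**Step 1: one full block.** Four intervention and two control places can be ordered in 15 equally likely ways. The next place is certain when only one arm is left in the block.

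| Place | Situation that makes it certain | Probability |
|---|---|---|
| 1, 2 | none | 0 |
| 3 | both controls in the first two | 1/15 = 6.7% |
| 4 | both controls in the first three | 3/15 = 20% |
| 5 | both controls in the first four (6/15), or four interventions (1/15) | 7/15 = 46.7% |
| 6 | always | 100% |

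The sum is 1/15 + 3/15 + 7/15 + 15/15 = 26/15 = 1.73 places of 6, or 28.9%. Of these, 1.33 are certain intervention and 0.40 certain control.

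**Step 2: the whole trial.** Eight per practice is one full block plus two places of the next, and those two are never certain. So 1.73 / 8 = 21.7%, and 5 × 1.73 = 8.7 of 40.

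**Step 3: other spreads over the practices.** 10/10/10/5/5 gives 7.5 of 40 (18.7%). 4/4/8/12/12 gives 9.2 (23.0%). 6/6/6/6/16 and 12/12/6/6/4 each give 10.7 (26.7%).

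**Step 4: guessing.** Always guessing intervention is right 66.7% of the time. Guessing the arm with more places left is right for 5.8 of 8, or 72.5%. That is 29.0 of 40 against 26.7, about 2.3 more correct guesses.

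**Step 5: varying block sizes.** Exact enumeration for eight participants in one practice. The guesser knows which sizes are possible (equally likely) but not the size in use.

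| Block sizes | Certain | Best guess correct |
|---|---|---|
| 6 only (the plan) | 21.7% | 72.5% |
| 3 and 6 | 7.5% | 73.1% |
| 6 and 9 | 4.7% | 70.9% |
| 3, 6 and 9 | 2.0% | 71.2% |
| unrestricted 2:1 | 0% | 66.7% |

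**The case against.** The case on the other side has several parts, and much of it stands.

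- **Concealment.** A reader might infer that concealment lapses at consent, because the Randomisation section says "Both the research team and participants will be unaware of the treatment allocation prior to consent". The text does not support that. The sentence before it already extends concealment to assignment. What remains is inference from past allocations, which neither sentence addresses.
- **Discretion.** A reader might infer that the team decides final eligibility after consent. In fact the inclusion and exclusion criteria are assessed at the screening call (Screening and informed consent, and Table 1). The later condition is a data-return rule, and prompting is described for all partial returners. Nothing says that the team judges borderline data or reorders a queue. With 40 participants over about eight months and five practices, entry is about one per practice per month if evenly spread, so a queue would be uncommon. Discretion at this step is therefore an opportunity, not something the text shows.
- **Extent.** It would be too strong to say that the next allocation is often known. About 78% of allocations are not certain. Most of the certain ones are intervention places, which anyone would guess at 2:1.
- **Reach.** Follow-up attendance is one rate over all randomised participants, so moving engaged people between arms barely changes it. Fidelity concerns the health professionals' delivery. The between-arm comparisons are secondary and stated to be unpowered.

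These arguments limit the size of the problem. They do not remove it, because the separate list-holder cannot prevent deduction from assignments already made.

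**Conclusion.** The point holds as a moderate weakness in the allocation procedure. About one allocation in five can be deduced with certainty: 21.7%, or 8.7 of 40, at eight per practice; 18.7% to 26.7% over the other spreads tried; 28.9% within full blocks. This rests on the team knowing the block size and following the assignments in each practice.

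Because randomisation depends on data returned after consent, that knowledge could influence who enters which arm. The secondary between-arm comparisons are the main exposure, and the app-use criterion a lesser one. The documents do not support reading this as a threat to the pooled follow-up rate, or as evidence that selection takes place.

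It is still worth correcting in a feasibility trial, because testing the trial procedures is one of its stated aims and a definitive trial could inherit them.

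**What to change.** 1. **Block sizes.** For participants still to be randomised, or otherwise in the definitive trial, use randomly varying block sizes compatible with 2:1, for example 3, 6 and 9, and do not tell the research team which are in use. Sizes 3 and 6 alone are a weaker choice, as the last table shows.
2. **Completeness log.** Require the team to record that a participant's baseline data are complete before it asks the independent researcher for the allocation. This matters at least as much as the block sizes, because varying them removes most of the certainty but little of the guessing advantage. The log makes entry decisions dated and auditable.

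**Cost.** Balance within practices becomes slightly looser. Trial status says that recruitment opened on 25 September 2018, so a change now means a small alteration to a sequence already in use; if that is unwelcome, it belongs in the definitive trial. The 2:1 ratio, the stratification by practice and the sample size stay as they are. Rewording the sentence that refers to consent is optional, because concealment up to assignment is already stated.

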### Blinding

It is not possible to blind the participants, the clinicians delivering the intervention or the research team to treatment group due to the nature of the intervention. The main trial outcomes are progression criteria and process measures, which are unlikely to be influenced by knowledge of treatment allocation. Intervention effectiveness measures comparing trial arms, which would be used as the primary outcome in a future RCT, are objectively measured outcomes and not open to interpretation by researchers.

### Primary outcomes

The primary objective of the trial is to determine whether to progress to a full trial or whether substantial amendments to the trial procedures are required. Based on previous trials of a similar nature we would hope to achieve 80% for the first two progression criteria. Allowing for the 95% confidence interval around this point estimate, we have set the minimum criteria for immediate progression at 65%.

Level one: the following criteria must be met to progress to a full trial with minimal amendments to trial procedures:
That 65% of participants attend the follow-up session.Healthcare professionals typically conduct a brief advice session where at least four out of six of the essential intervention elements are present, assessed by comparing the delivered intervention against a checklist of the components required by the protocol, using audio recordings of the consultation.At least 50% of participants use the app to scan products on at least one occasion by the end of month one.

Level two: the following criteria must be met to continue to a full trial with substantial amendments to trial procedures:
At least 40% of participants attend the follow-up session.Healthcare professionals typically conduct a brief advice session where at least a mean of three out of six of the essential elements are present.At least 40% of participants use the app to scan products on at least one occasion by the end of month one.

If level-two criteria are not met, it would not be considered feasible to continue to a full trial with this trial design.

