### Intervention and comparator

#### Intervention

This study investigates the Salt Swap intervention, which aims to help people swap to lower-salt alternatives for everyday foods when grocery shopping. The intervention development was informed by two established behaviour change frameworks, the Behaviour Change Wheel [24] and the Theoretical Domains Framework (TDF) [25]. These theoretical frameworks were used to identify the key determinants of behaviour, particularly the aspects of capability, opportunity and motivation, that need to be influenced in order to support people to reduce purchases of high-salt foods and drinks. The intervention development is described elsewhere.

The intervention incorporates motivation and education, problem solving, goal setting and action planning. It comprises two main components: brief advice provided by a healthcare professional (HCP) at the GP practice and instructions to use the Salt Swap app. Healthcare professionals, typically practice nurses or healthcare assistants, will be trained by one face-to-face training session with a researcher and by video-based training materials. The content of the 20-min one-to-one advice session is based on best practice guidance and information by expert sources including NHS Choices and the British Heart Foundation (BHF) [26, 27]. It is supported by the Salt Swap booklet given to participants during the intervention visit.

This advice incorporates information on:
The impact of salt on health and blood pressure in particularThe health benefits of salt reductionRecommended salt intakeAdvice for cutting salt intakeExamples of lower-salt alternativesSalt reduction goal settingSelf-assessmentAction planning to reduce salt intake

In addition, during this session participants are encouraged to download a novel mobile phone app, Salt Swap, which delivers tailored, salient information on the salt content of products. Users scan a product barcode to receive nutritional information, presented using the traffic light labelling system recommend for use in the UK [28], and are shown suggested lower-salt alternatives. The app contains a database of food and drinks available in UK supermarkets and their nutritional composition. The app allows users to set goals for salt reduction and to receive feedback on the achievement of these goals and the salt reduction achieved through swapping to lower-salt products (see Fig. 1). All other clinical care will continue as usual.

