#### Process measures

The process measures will be:
Recruitment rates: total recruited and number per practice per month, (including the number invited who were eligible and consented, and the number of recruited participants that completed all baseline assessments and were randomised).Acceptability of the intervention delivery. The perspective of the healthcare professionals responsible for delivering the intervention will be captured via interviews, exploring barriers to and facilitators of delivery and their confidence and belief in their capability to deliver the intervention session.App use and acceptability; measured quantitatively through within-app automatic recording (e.g. frequency of use, number of products scanned per user, frequency of swaps presented and accepted, use of specific behaviour change functionality such as goal setting), and measured qualitatively through the post-intervention survey and think-aloud accompanied shopping trips.Feasibility of data collection: willingness of participants to submit 24-hour urine samples and completeness of shopping data (including completeness of data on the salt content of purchased foods).Evidence of contamination; measured as use of the Salt Swap app by the control group.Changes in participant knowledge, perceptions and behaviours in relation to salt intake and health, measured qualitatively through participant questionnaires and semi-structured interviews.

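### The app-use progression criterion counts a scan made during a researcher-accompanied shop, and part of the accompanied-shop window can lie inside month one

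*Protocol article*

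**What the plan says.** Under Primary outcomes, app use is one of three criteria for deciding whether to go on to a full trial. The requirement is that participants "use the app to scan products on at least one occasion by the end of month one": at least 50% of them for level one and at least 40% for level two. Neither level says which event starts month one, and neither sets aside scans made in a researcher's company.

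Table 1 counts weeks from baseline: allocation at week 2, intervention at weeks 2–3, accompanied shop at weeks 4–9, follow-up at weeks 9–10. The Accompanied shop section describes a think-aloud trip with a convenience sample from both arms. Part of its purpose is "to assess the barriers to and facilitators of using the Salt Swap app". On timing it says: "This qualitative assessment will be undertaken at staggered time points throughout the study". It gives neither the number of trips nor their split by arm. The Data management section confirms that a researcher conducts them.

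The Intervention section names two main components: the brief advice from a healthcare professional and the instructions to use the app. The accompanied shop is not among them. App use is also a process measure, "measured quantitatively through within-app automatic recording".

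**The concern.** The criterion is meant to show whether people given the intervention take up the app. One scan is enough to be counted, and the status cannot be lost afterwards. A think-aloud trip that is partly about this app, with a researcher present, is an obvious occasion for a first scan. If that scan falls inside month one, the participant counts as a user even if the app would otherwise have gone unused. The count then partly measures a research procedure.

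The Blinding section argues that the progression criteria are unlikely to be affected by knowing the allocation. That does not cover a researcher being present when the counted behaviour happens.

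At stake is the choice between going on with minimal changes, going on with substantial changes, and stopping. For app use, the first two levels are 10 percentage points apart in an arm of about 27 people.

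**Working it through.** **The plan's own figure.** The protocol gives no precision figure for app use. Its only one, in Sample size, is an 80% follow-up rate estimated to within 12 points with 40 participants. It reproduces: 1.96 × √(0.8 × 0.2 / 40) = 0.124, so 67.6% to 92.4%. This point does not affect it.

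**Step 1: overlap of the two windows.** From Table 1, the shop window is weeks 4–9, which is 5 weeks long. Take a month as 4 weeks, or as 30.4/7 = 4.34 weeks.

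| Month one starts at | Ends at week | Overlap with weeks 4–9 | Share of 5 weeks |
|---|---|---|---|
| Intervention, week 2 | 2 + 4 = 6.00 | 2.00 weeks | 40% |
| Intervention, week 2 | 2 + 4.34 = 6.34 | 2.34 weeks | 47% |
| Intervention, week 3 | 3 + 4 = 7.00 | 3.00 weeks | 60% |
| Intervention, week 3 | 3 + 4.34 = 7.34 | 3.34 weeks | 67% |
| Baseline, week 0 | 4.34 | 0.34 weeks | 7% |

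Counting from the intervention visit is the natural reading. A month counted from baseline would leave only 4.34 − 3 = 1.34 to 4.34 − 2 = 2.34 weeks with the app.

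**Step 2: distance between the levels.** Forty participants randomised 2:1 give about 27 in the intervention arm. With 27 as the denominator (an assumption, see below):
- level one: 0.50 × 27 = 13.5, so 14 users
- level two: 0.40 × 27 = 10.8, so 11 users
- difference: 3 people, at 1/27 = 3.7 points each

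**Step 3: what a few accompanied shops could do.** Let q be the true unaided share of users and k the number of intervention participants accompanied within month one. Suppose that all k scan on the trip and that they are otherwise typical of the arm. The probability of reaching level one is then P(X ≥ 14 − k), with X binomial on 27 − k trials with probability q.

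| q | k = 0 | k = 2 | k = 4 | k = 6 |
|---|---|---|---|---|
| 0.30 | 0.014 | 0.044 | 0.120 | 0.277 |
| 0.40 | 0.145 | 0.268 | 0.444 | 0.650 |

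The expected rise in the observed share is k(1 − q)/27. At q = 0.40 this is 2 × 0.6/27 = 4.4 points for k = 2, 8.9 points for k = 4 and 13.3 points for k = 6. Both k and q are illustrative, since the protocol gives neither. For a given k these are upper bounds, because every accompanied participant is taken to scan.

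**Denominator.** The Progression criteria paragraph of the planned analysis uses all randomised participants, although only the intervention arm is given the app. On a denominator of 40 the levels would need 20 and 16 users out of about 27 (74% and 59%), four people apart. The mechanism is the same.

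**The case against.** The strongest reply has four parts.

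- **The shop is observation.** Its first stated aim is wider than the app, it covers both arms, and nothing says that the researcher asks for a scan. A non-user explaining why the app stays unused would also serve the aim. This stands: that the trip converts non-users is an inference about how people behave when watched, and the protocol does not state it. What the protocol does fix is that such a scan would count.
- **The size has no basis in the document.** This stands in full. Few intervention participants may be accompanied, control trips should add no users, and volunteers may have been scanning already.
- **Other data would reveal it.** The process measures include frequency of use and products scanned per user, so people with a single scan would be visible, and app use alone cannot trigger progression. This softens the consequence. The criterion as written would still be scored with those scans included.
- **Which log entries count can be left to the full protocol or analysis plan.** This stands only in part. The article itself fixes the criterion, its thresholds, its time limit and the visit window that overlaps it, and the problem lies in how these combine.

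Two stronger readings are tempting. A reader might infer that accompanied shops as a whole fall inside month one. Table 1 and the staggered timing do not support that: only part of the window overlaps, and about 7% of it if the month runs from baseline. A reader might also infer that the app is first opened, or a product first scanned, with the healthcare professional. The text says only that "during this session participants are encouraged to download a novel mobile phone app". It describes neither opening the app nor scanning in that session, so this remains a possibility that is not excluded.

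**Conclusion.** The point holds in limited form. As written, one scan on a researcher-accompanied shop satisfies the app-use criterion. If month one runs from the intervention visit, 40–67% of the accompanied-shop window lies inside it, so such scans can enter a primary outcome. Any effect on the count is upward.

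The size is unknown. It depends on how many intervention participants are accompanied within month one and how many of them would not otherwise have scanned, and the protocol gives neither. What can be said is that, on a denominator of about 27, three converted non-users cover the distance from 11 to 14 users. A definite inflation in percentage points cannot be claimed. That a full trial would have no accompanied shops is also an inference, drawn from their not being a component of the intervention.

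This is a cheap improvement to the definition. It does not show that the criterion is unusable.

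**What to change.** In Primary outcomes, state that month one runs from the intervention visit. Define a user as a participant with at least one scan in that month on a day other than an accompanied-shop day, taken from the in-app log. Report the share based on all scans beside it.

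The cost is a sentence or two of text and a date filter. A criterion with a time limit already needs dated scans, so the only addition is the date of each accompanied shop. The downside is that a participant whose only scans were on the accompanied shop counts as a non-user, even if that first use was genuine, so the figure may be slightly less favourable. Showing both figures makes the difference visible.

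Two wider changes are not recommended. Excluding the whole day of the advice session would discard genuine use by someone who shops straight after the visit. Moving all intervention-arm shops past month one would conflict with the staggered timing and lose observation of early use.
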